#### Implementation

The allocation sequence follows successive numbers from 1 to 200. Participants may be enrolled by every study team member based on the previously described schedule. After consent is given, the sealed envelope that contains the corresponding allocation number is then handed over to the nurse who prepares the study drug. Preparation study drug(s) is controlled by a member of the study team who is not involved in the recruitment process or the follow-up of the specific study participant. The study drug is then administered by the anaesthesiologist who also is not member of the study team. All scheduled delirium assessments, except for the MMSE, are performed by the nurses responsible for the care of the study participant except. The MMSE is conducted by a member of the study team.

### Blinding

Trial participants and care providers including the anaesthesiologist administering the study drug are blinded. The study drugs are prepared as follows to avoid assumption by any colour difference from the placebo (see Table 2 for weight dependent dosing). This adds to a total of 40 ml solution administered slowly to every patient:Trial arm haloperidol: one 20 ml syringe containing the appropriate concentration of haloperidol, and one syringe containing 20 ml NaCl 0.9%Trial arm ketamine: one 20 ml syringe containing the appropriate concentration ketamine, and one 20 ml syringe containing NaCl 0.9%Trial arm haloperidol + ketamine: one 20 ml syringe containing the appropriate concentration haloperidol, and one 20 ml syringe containing the appropriate concentration ketamineTrial arm placebo: two syringes, each containing 20 ml NaCl 0.9%

### Data collection

All participants in the study will be provided a participant information sheet describing the study and providing sufficient information to enable the participant to make an informed decision about their participation in the study. The patient information sheet and the consent form will be submitted to the competent ethics committee to be reviewed and approved. The formal consent of a participant, using the approved consent form, must be obtained before the participant is subjected to any study procedure. The participant should read and consider the statement before signing and dating the informed consent form and should be given a copy of the signed document. The consent form must also be signed and dated by the investigator (or his designee). The signed form will be retained as part of the study records.

The patient will be informed on the possibility to withdraw their data from the study at any time and without needing to provide any explanation. In the case of discontinuation from trial participation, the data collected (i.e., measured laboratory values) will be used for publication if the patient does not object. In the case of deviation from the study protocol, patient data will be destroyed and thus not used for publication. Patients discharged from the hospital before the 3-day follow up post-surgery will be contacted by phone to assess their wellbeing. The collected data will be used for publication in these cases.

Data will be entered into a web-based electronic case report form (eCRF) established by the CTC Zurich (secuTrial®). Paper case report forms will be used in parallel also because of possible technical difficulties. Trial staff will have exclusive access 24 h per day, 7 days per week, to the electronic case report for data entry. A unique patient identification code will be assigned electronically to every randomised patient.

#### Trial medication

Patients enrolled in the trial will be randomised to receive either haloperidol (Haldol®, concentrated 5 mg/ml for intravenous (iv) administration, Janssen-Cilag AG, Zug, Switzerland), ketamine (Ketalar®, concentrated 50 mg/ml for iv administration, Pfizer AG, Zurich, Switzerland), both drugs combined or NaCl 0.9% (NaCl 0.9% B. Braun® for iv administration, B. Braun Medical AG, Sempach, Switzerland) administered right before induction of anaesthesia to prevent postoperative delirium.

#### Delirium assessment tools

For delirium assessment, the MMSE, DOS and Nu-DESC will be assessed preoperatively to avoid inclusion of patients suffering from cognitive decline prior to surgery. These three tests will be assessed daily one first 3 postoperative days to document the course after surgery and to detect the potential development of postoperative delirium. The MMSE and Nu-DESC will be assessed once daily, and the DOS will be assessed during every nursing shift. Data collection forms are available online in German and English.

The MMSE score is an assessment tool used in nearly all medical fields. The MMSE is a 30-item checklist of symptoms suggestive of cognitive decline. Patients lose 1 point for each symptom that manifests during the specified time frame: 1 point is taken if the question cannot be answered, if it is answered incorrectly or if the demanded task cannot be executed by the patient. Overall, orientation in time and place, retentiveness, short-term memory, language and text comprehension, presence of agraphia, apraxia, agnosia, and executive functions (e.g., action planning) are evaluated. A total of 30 points can be achieved. No cognitive decline is suspected in patients who achieve 27 points. A total of 26 points is considered the threshold value. A total MMSE score of fewer than 24 points is indicative of cognitive limitations. Therefore, patients with an MMSE score below 24 points or a DOS score of at least 3 points preoperatively are not recruited for the study.

The DOS represents a screening tool that has been specifically developed for the assessment of conspicuous behavioural traits suggestive of cognitive decline by the nursing team responsible for the care of a patient. It is based on observations made according to a 13-item checklist that is used during every shift, usually over a period of 3 days. In our study, the DOS score is assessed preoperatively and on postoperative days 1–3. One condition for DOS score interpretation is the assessment of an additional tool for the estimation of cognitive function when the DOS score suggests cognitive decline (i.e., DOS score ≥ 3 points) [19].

The Nu-DESC is a delirium screening tool that has been translated into German in accordance with the guidelines [20]. Based on the Nu-DESC assessment tool, Gaudreau et al. have developed an easy-to-use, nursing-based measurement tool that can be easily integrated in everyday practice [20].

If the patient has to be treated in the ICU after surgery, the ICDSC score is documented during every shift. The ICDSC is among the most well-studied and widely implemented adult ICU delirium screening tools worldwide and has been recommended by recently updated clinical practice guidelines. The ICUs of the University Hospital of Basel routinely use the ICDSC for assessment of delirium. Based on high-quality evidence, it has been recommended for the screening of delirium in ICU by the Society of Critical Care Medicine [7]. A score ≥ 4 indicates a positive ICDSC and the presence of delirium [7, 21].

#### Laboratory assessments of cognitive function

##### NSE

Elevated NSE can be measured in the blood (half-life of roughly 48 h) or the cerebrospinal fluid (half-life of 6–8 h) and is indicative of various pathological conditions. It serves as a marker of acute neuronal lesions as in anoxia, acute brain injury, or inflammatory processes leading to cell destruction. NSE levels are negligible after damage to extracerebral tissue. NSE is quantified in acute brain injury, subarachnoid haemorrhage, stroke, status epilepticus, dementia, active multiple sclerosis, severe central nervous system (CNS) infection, decompensated hypertension, intracerebral and extracerebral neoplasia, cardiopulmonary bypass during heart surgery, cardiac arrest, and neurological metabolic diseases for course documentation and prognostic evaluation.

Although elevated NSE is associated with above-mentioned conditions, Rasmussen et al. identified a significant decrease in NSE after abdominal surgery in a study of 65 patients, but this did not correlate with cognitive dysfunction [22]. Other studies with larger cohorts also showed no difference in NSE levels in delirious and non-delirious patients after investigation of elderly patients who were acutely admitted after hip fracture [23]. However, other data suggest correlation between elevated NSE and delirium in the ICU population [24]. We conclude that the role of NSE in the diagnosis of delirium and its possibility to evaluate long-term outcome is still unclear and needs further investigation.

##### S-100β

S-100 proteins play a role in the regulation of various cellular processes (e.g., cell cycle progression and differentiation) and can be localised in the cytoplasm and/or nucleus of numerous types of cells [25]. Altered levels have been connected to several diseases including Alzheimer’s disease [26], Down’s syndrome [27], epilepsy [28, 29], amyotrophic lateral sclerosis [30, 31], melanoma [32–34], type I diabetes [35, 36] as well as in several neurological [37] and neoplastic diseases [38].

Study results on S-100β are also inconclusive for delirium. A study interpreted elevated levels of S-100β as either a marker of cerebral damage or as a consequence of delirium or cerebral damage that could lead to delirium [23]. While delirious patients in this study had the highest levels of S-100β, calling for further investigation to elucidate its role in the pathophysiological pathway that leads to delirium [23], another study found no significant difference in S-100β in delirious compared to non-delirious patients but this was specifically in a critically ill cohort [24]. To resolve this uncertainty, we would like to profoundly investigate this marker in postoperative delirium.

##### Cortisol

Serum cortisol levels have been shown to correlate with both the degree of delirium and the risk of developing it, as stress was found to play a major role in delirium and its pathogenesis postoperatively [39]. Serum cortisol has been suggested to be an important marker of risk of postoperative delirium after cardiac surgery in patients with a preoperative diagnosis of major depressive disorder [40].

Serum cortisol levels depend on the patients’ perioperative stress levels. To date, there remains no clear definition of physiological vs. pathological serum cortisol levels following a certain type of surgery. The present study will analyse cognitive decline or present delirium based on the mentioned scores and correlation between serum cortisol levels preoperatively vs. postoperatively.

#### Electrocardiogram

To evaluate the possible consequences of a potential side effect of haloperidol (i.e., prolongation of the QT interval), we will record an ECG preoperatively and 48 h after surgery. One study demonstrated QT prolongation after intravenous administration of haloperidol to be moderately correlated with the dose administered and recommends clinicians to be aware of this correlation [41]. It is recommended that haloperidol should be discontinued if QTc exceeds 500 ms due to elevated risk of arrhythmia (e.g., torsade de pointes) [42]. Since the elimination half-life is estimated to be 20 h, we will repeat the ECG 48 h after surgery to protect patient safety.

### Data management

All data from this study will be kept within the Trial Master File, and only the study team will have access. In case of a patient’s retroactive denial of study participation, the data collected will not be used for publication in the present or in future trials. In such cases, the data will be destroyed.

All study data will be archived in a designated place on the Surgical Intensive Care Unit at the University Hospital of Basel for a minimum of 10 years after study termination or premature termination of the clinical trial. We plan to store the data also within an eCRF.

### Statistical methods

#### Null and alternative hypothesis

The two-sided statistical null hypothesis will test whether the preoperative administration of haloperidol, ketamine or both drugs combined immediately before induction of anaesthesia compared to placebo is unable to prevent the decline of postoperative cognitive function. The alternative hypothesis is that there is an effect of one of the drugs or the combination.

#### Planned analyses and sample size rationale

##### Primary analysis

Differences among the four groups will be analysed by the chi-square test. Post hoc the groups will be compared by pairwise chi-square test including the Bonferroni correction.

We will follow the intention-to-treat principle. Data on all study participants who have received the study drug as part of one of the four treatment arms will be analysed.

When the sample size in each of the four groups is 50, the 0.05-level chi-square test will have 80% power to detect a difference in proportions characterised by variance (V) of proportions:

V = Σ(π_i_- π_0_)^2^/G of 0.0125 and an average proportion of 0.35

Since study participants will be excluded from the primary analysis if there is a significant decline in MMSE score of at least 2 points during at least 1 of the 3 postoperative days or if they are treated in the ICU after surgery. The determined sample size following power analysis will be increased (see above). This might lead to an uneven number of study participants distributed over the four treatment arms after termination of the study, an occurrence that will need to be taken into consideration.

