#### Exclusion criteria

Participants meeting the following criteria are excluded from the study:Delirium upon hospital admission or during the course of the hospital stay or Mini Mental State Examination (MMSE) score < 24 points or a Delirium Observation Screening Scale (DOS) score ≥ 3 pointsDementiaHigh risk of postoperative treatment in the intensive care unit (ICU) (standard procedure excluded)Known haloperidol or ketamine intoleranceLack of cooperation or lack of communication possibilities○ Speech disorders○ Isolation○ Aphasia○ Coma○ Terminal illness○ Drug or alcohol abuseQT interval (QTc) prolongation (≥ 460 ms in men, ≥ 470 ms in women) or drugs influencing QT interval (see Appendix)Parkinson’s diseaseParkinsonismIntake of dopaminergic drugs (levodopa, dopamine agonists)EpilepsyDelay of surgery for > 72 h after set indication for surgeryBody weight > 100 kgPatient is unable to read German

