### Outcomes

#### Primary outcome measure

Superiority of one of the active comparator treatment arms in patients after surgery for prevention of hypoactive, hyperactive or mixed delirium, which is assessed by 2-point drop in MMSE score when assessed during one of the 3 postoperative days.

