#### Handling of missing data and drop-outs

Data from study participants who have received the study drug as part of one of the four treatment arms and who were assessed for delirium as declared and who have not been treated in the ICU following surgery can be integrated in the analysis of the primary endpoint. All missing data will be documented in the CRF and described in detail within the publication. Missing values on the secondary endpoint will not be assigned (complete case analyses).

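### The Primary analysis section excludes participants with a postoperative MMSE decline of at least 2 points, which is the primary event itself, and so contradicts the rest of the plan

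*Protocol article*

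**What the plan says.** Under Primary outcome measure, delirium is the event, "which is assessed by 2-point drop in MMSE score when assessed during one of the 3 postoperative days".

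Under Primary analysis, the article makes four statements that bear on who is analysed:

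- The test: "Differences among the four groups will be analysed by the chi-square test", followed by Bonferroni-corrected pairwise tests.
- The population: intention-to-treat is declared, and "Data on all study participants who have received the study drug as part of one of the four treatment arms will be analysed".
- The power: "When the sample size in each of the four groups is 50, the 0.05-level chi-square test will have 80% power", for V = 0.0125 and an average event proportion of 0.35.
- The exclusion: "Since study participants will be excluded from the primary analysis if there is a significant decline in MMSE score of at least 2 points", continuing "during at least 1 of the 3 postoperative days or if they are treated in the ICU after surgery".

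The exclusion sentence opens with 'Since' and has no main clause. The text after it uses the exclusion to justify enlarging the sample and to warn of uneven arms.

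Under Handling of missing data and drop-outs, the primary endpoint analysis takes participants who received study drug, "who were assessed for delirium as declared and who have not been treated in the ICU following surgery can be integrated in the analysis". No MMSE exclusion appears there. The Sample size section under Methods gives 188 participants for power 0.8, raised to 200 for drop-outs.

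**The concern.** The exclusion and the endpoint use the same instrument, the same 2-point threshold and the same three-day window. The word 'significant' in the exclusion has no definition apart from the 2 points, so it does not separate the two. If the endpoint is read as a drop of 2 points or more, the excluded group and the event group are identical. If it is read as a drop of exactly 2 points, the events still all lie inside the excluded group.

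At stake is the composition of the primary analysis set. A literal reading leaves nothing to compare. A partial or case-by-case reading decides who is analysed according to the outcome, which undoes the protection of randomisation. If the text is not settled before the allocation is known, the choice could be made with the results in view.

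**Working it through.** **Inputs.** From Primary analysis: 50 per group (N = 200), G = 4, alpha 0.05, V = 0.0125 (divisor G), average proportion p = 0.35. From Sample size: 188 before and 200 after the drop-out allowance.

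**1. Reproduce the stated power.** For the four-group chi-square test with 3 degrees of freedom, the non-centrality parameter is

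N × V / [p(1 − p)] = 200 × 0.0125 / (0.35 × 0.65) = 2.5 / 0.2275 = 10.99.

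Power at the 0.05 level is 80.3%, which matches the stated 80%. A parameter of 10.90 gives exactly 80%, so the N needed is 10.90 × 0.2275 / 0.0125 ≈ 198.4. The calculation therefore assumes that about 35% of the *analysed* participants have the event.

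**2. Apply the exclusion literally.**

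| Recruited | Events at 0.35 (all excluded) | Left in analysis | Events left |
|---|---|---|---|
| 200 | 70 | 130 | 0 |
| 188 | 65.8, about 66 | about 122 | 0 |

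Every arm shows 0/n. The expected event counts are 0, so the chi-square statistic is undefined for the four-group test and for each pairwise test. The power statement and the exclusion cannot both hold.

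**3. Compare with the allowance.** The increase from 188 to 200 is 12 participants, or 12/200 = 6%. Removing 35% would take about 70. Keeping 188 after such a loss would need 188 / 0.65 ≈ 289 recruits. The allowance was not sized for this exclusion.

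**4. Compare the statements on the analysis set.**

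| Place | Participant with MMSE decline ≥ 2 | Participant treated in ICU |
|---|---|---|
| Primary outcome measure | is the event | not mentioned |
| Primary analysis, intention-to-treat statement | analysed | analysed |
| Primary analysis, power statement | counted (0.35) | not mentioned |
| Primary analysis, exclusion sentence | excluded | excluded |
| Handling of missing data and drop-outs | not excluded | excluded |

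The MMSE exclusion stands alone against every other statement. The ICU exclusion appears twice, so it looks deliberate, but it depends on a post-randomisation event and conflicts with the intention-to-treat statement.

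**5. Partial application.** Suppose a fraction q of events is removed equally in two arms. Each arm's odds are multiplied by (1 − q), so the odds ratio does not change. With assumed proportions 0.50 and 0.30 and q = 0.5:

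- 0.50 becomes 0.25 / 0.75 = 0.333, and 0.30 becomes 0.15 / 0.85 = 0.176.
- Odds ratio: 0.43 before and after.
- Risk ratio: 0.60 becomes 0.53, further from 1.
- Risk difference: 0.20 becomes 0.16, nearer 0.

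If the fraction differs by arm, the bias can go either way.

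**6. With the MMSE clause removed.** At V = 0.0125 and p = 0.35, power is 80.3% with 200 analysed, 77.6% with 188, 75.6% with 180 and 70.0% with 160. The article gives no ICU treatment rate, so the numbers below 188 are assumptions.

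**The case against.** The strongest reply is that one broken sentence should not outweigh the rest of the plan. The intention-to-treat statement, the 0.35 proportion, the set described under Handling of missing data and drop-outs, and the 12-person allowance all imply that events are counted. This stands. A reader might infer that the trial will be analysed with no events, or that its power is zero. The documents do not support that: the zero-event result follows from one clause and from nothing else in the article.

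The reply does not remove the problem. The article uses that clause as a working reason for the larger sample and the possible imbalance between arms, and nothing in it says which statement prevails. Nor is this a matter of detail left to a fuller document, because the rule is stated and it is wrong.

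Two further inferences fail:

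- *That partial application would pull every comparison towards no difference.* Step 5 of the working shows an unchanged odds ratio and a risk ratio further from 1 under equal removal. Under unequal removal the direction is open.
- *That the eligibility criterion on delirium "upon hospital admission or during the course of the hospital stay" also removes postoperative events.* It is a screening criterion listed beside the MMSE and DOS thresholds. The sections Delirium assessment tools and Population make clear that these concern cognitive impairment before surgery.

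**Conclusion.** The contradiction is real and affects the primary analysis set. Read literally, the exclusion sentence removes all primary events, about 70 of 200 (66 of 188) if the planning proportion of 0.35 holds, and leaves a test that cannot be computed. It is incompatible with the endpoint definition, the intention-to-treat statement, the power calculation, the missing-data section and the size of the drop-out allowance. The most likely explanation is a drafting error, but the article does not say what was intended.

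That the MMSE rule and the event coincide needs no numerical assumption. Only the count of 70 or 66 rests on the 0.35. Partial application would condition on the outcome, with bias that cannot be signed in advance. Because this is the primary analysis, it must be corrected before the allocation is revealed.

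**What to change.** Before unblinding:

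1. Delete the MMSE-decline clause from the exclusion sentence under Primary analysis, and complete or remove the rest of that sentence.
2. State that participants with a postoperative MMSE decline of at least 2 points on any of the three days count as primary events.
3. Describe one primary analysis set, in the same terms, under Primary outcome measure, Primary analysis, and Handling of missing data and drop-outs.
4. Settle the ICU exclusion in the same correction. Either keep ICU-treated participants in the primary analysis, as the intention-to-treat statement requires, or keep the exclusion, stop calling the analysis intention-to-treat, and justify a set defined after randomisation. Deleting the MMSE clause alone would leave the section contradicting itself.

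The cost is a wording correction, with no additional patients or procedures. The article's section on deviations from the statistical analysis plan requires substantial deviations to be reported to the Ethics Committees, and all deviations to be listed and justified in the final statistical report. If the correction counts as substantial, that notice is part of the cost. The Trial status section reports 171 patients recruited by August 2017 and final results expected in the first half of 2018, so the time to make the correction before unblinding is short.
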